## Abstract

**Background:**

Same-sex attracted young adults have been found to experience higher rates of mental health problems and greater difficulties in accessing specialist mental health care services compared to their heterosexual peers. Internet-based mental health interventions have the potential to be more engaging and accessible to young adults compared to those delivered face-to-face. However, they are rarely inclusive of lesbian women and gay men. Thus, the current study aims to evaluate the effectiveness of an online mental health and wellbeing program, *Out & Online* (http://www.outandonline.org.au), in comparison to a wait-list control group, for reducing anxiety and depressive symptoms in same-sex attracted young adults aged between 18 and 25 years.

**Methods/Design:**

We are recruiting, through media and community organisations, 200 same-sex attracted young adults with anxiety and/or depressive symptoms and mild to moderate psychological distress (Kessler-10 score between 16 to 21). Participants will be randomly allocated to the intervention (the online program) or the wait-list control group based on a permuted blocked randomisation method to allow for stratification by gender. Participants in the intervention group will receive a tailored program for up to three types of mental health difficulties simultaneously. The primary outcome of anxiety and/or depressive symptoms, and secondary outcomes related to psychological distress, wellbeing and health behaviour will be measured at pre-intervention (0 week), post-intervention (8 weeks) and at a 3-month follow-up (20 weeks).

**Discussion:**

This online mental health and wellbeing program will be one of the first online interventions to be designed specifically to be relevant for same-sex attracted individuals. If the program is found to be effective it will improve access to specialist same-sex attracted-relevant mental health services for young adults and will facilitate wellbeing outcomes for these individuals. This program will also be a significant development in the delivery of tailored interventions that target multiple types of mental health conditions simultaneously.

**Trial registration:**

Australian New Zealand Clinical Trials Registry: ACTRN12611000700932. Date registered: 7 July 2011.

## Background

Poor mental health has been identified as a key issue for same-sex attracted young adults (SSAYA). Research indicates that SSAYA are twice as likely to attempt suicide as peers with opposite-sex attractions [1–4], 3.5 times more likely to engage in self-harm and 5 times more likely to report suicidal ideation than their heterosexual peers [5]. SSAYA also experience more depressive symptoms compared with heterosexual youth [3, 6–10]. In addition, 9% of SSAYA have been found to meet criteria for the diagnosis of posttraumatic stress disorder (PTSD) [11], and social anxiety has been identified as a potential mental health problem among SSAYA as they learn to fear and avoid social situations [12].

The prevalence of mental health problems among SSAYA has been strongly linked to the experience of homophobia [13–15]. Homophobic attitudes give rise to prejudice, victimisation, physical and verbal abuse, harassment, and rejection of SSAYA within their home [16], school environment [17–19] and the wider community [11, 15]. These discriminatory behaviours result in stigmatisation, alienation and isolation among SSAYA, which, in turn, is related to depression, PTSD, social anxiety disorder (SAD) and suicidal ideation [20, 21]. In addition, the mental health of SSAYA can be influenced by internalised homophobia [14, 22], which refers to the extent that a same-sex attracted individual has internalised society's negative perceptions of homosexuality [23]. It has been proposed that internalised homophobia is experienced to varying degrees by almost all SSAYA raised in a society where heterosexuality is the sexual norm [16]. Internalising homophobic attitudes can lead to diminished self-concept and self-esteem [24]. Further, models of identity development propose that the adoption of a positive identity depends upon resolving internalised homophobia [25, 26].

In addition to higher rates of mental health problems compared to heterosexual youth and young adults, SSAYA also face greater barriers to accessing help such as feeling that mental health care services marginalise them by assuming heterosexuality and do not adequately assist them to address challenges unique to being same-sex attracted such as stigma and 'coming out' [27]. These barriers are intensified for SSAYA living in rural or regional areas where they have less access to relevant information, resources, support and services than their city peers. Evidence indicates that rural SSAYA attempt suicide six times more often than the population average [28] and experience higher levels of homophobia than their city peers [29]. Indeed, research with same-sex attracted adults living in rural areas indicates that most do not disclose their sexual orientation, that non-disclosure exacerbates social isolation, and that those who do disclose are vulnerable to homophobic responses from workers in the health care system [30].

### The role of the Internet for the delivery of mental health care

Given the difficulties that ‘at-risk’ SSAYA perceive in accessing mental health care services, particularly in rural and regional areas, the Internet may be an ideal way to deliver mental health interventions to this population [31]. The Internet has the potential to overcome a number of the structural and attitudinal barriers that often avert efforts to seek help, especially within rural and regional areas, including stigma, a shortage of trained health professionals and geographic and social isolation [32–35]. Previous research with adults, including young adults and those in rural and regional areas, has indicated that delivering interventions via the Internet provides flexibility, anonymity, and enhanced accessibility [36, 37]. Moreover, a web-based intervention is likely to be more engaging for young people who are early adopters of new technology [38]. Most young people, including those from disadvantaged backgrounds, have access to an Internet-enabled computer, with approximately 95% of 15 to 25-year-olds using the Internet [39].

Numerous Internet-based mental health interventions targeting young people have been developed and evaluated; for examples, see references [40–44]. These findings support the development and provision of Internet-based mental health programs for education about, and prevention and treatment of, a number of psychological symptoms and conditions experienced by young people [45]. In particular, online delivery of cognitive behaviour therapy (CBT) has been found to be effective in reducing symptoms of anxiety and depression [36].

Despite the evidence for online interventions and their potential for assisting SSAYA with mental health difficulties the majority are not specifically relevant to the needs of same-sex attracted individuals. In a review of 24 web- and mobile phone-based online interventions, Rozbroj *et al*. [27] concluded that online interventions seldom addressed the stressors faced by same-sex attracted individuals and contained content assuming or suggesting users were heterosexual.

### Online multi-symptom mental health and wellbeing program development

Given the need for online interventions relevant to SSAYA we developed an online CBT intervention (the *Out & Online* program, http://www.outandonline.org.au) designed to reduce anxiety and depressive symptoms and enhance wellbeing in SSAYA aged 18 to 25 years. The program was made relevant to SSAYA by using inclusive language and content (for example, pictures and videos depicting people in same-sex relationships), applying some of the strategies to stressors unique to being same-sex attracted (for example, 'coming out', feeing accepted by heterosexual peers and enhancing self-esteem and self-acceptance in the face of homophobia and internalised homophobia), and providing information on support services specialising in supporting same-sex attracted individuals.

### Study aims

The present study aims to evaluate via a randomised controlled trial (RCT) the *Out & Online* program in SSAYA aged between 18 and 25 years recruited via media and community organisations. The program will deliver symptom-relevant material across up to three different types of mental health difficulties (out of generalised anxiety, social anxiety, posttraumatic stress, obsessions and/or compulsions, panic and depressive symptoms) so as to present individual users with a customised mental health early intervention that respects their individuality, and acknowledges the reality and frequency of comorbid symptomatology.

The primary aim of the study was to examine the effectiveness of the *Out & Online* program for reducing anxiety and depressive symptoms and improving wellbeing. It was anticipated that additional benefits participants might gain from the program would include reduced internalised homophobia, more positive attitudes towards seeking help, greater sense of control over their health and greater satisfaction with their lives.

## Methods/Design

### Study design

This study will evaluate the intervention using an RCT. Participants meeting inclusion criteria and who have provided informed consent to participate will be randomly allocated to receive the intervention immediately or after a 20-week waiting period. Primary and secondary outcomes will be assessed via online surveys obtained from participants at pre-intervention (week 0), while completing the online program (weeks 2, 4 and 6), post-intervention (week 8) and 3-month follow-up (week 20). Figure 1 shows a flow chart of participant involvement in the RCT.

**Figure 1 Fig1:**
[figure not shown]
**Flow chart of the study design.**

### Participants

We will recruit participants through Australian organisations that work with SSAYA, mental health organisations, advertising via social, online and news media, and information sessions to community groups (including support groups for SSAYA, health professionals that work with SSAYA).

Inclusion criteria are: Australian resident, aged between 18 and 25 years, same-sex attracted (self-identify as gay, lesbian or bisexual), access to the Internet, mild to moderate psychological distress (Kessler-10 score between 16 and 21) and having depressive and/or anxiety symptoms (being eligible to receive tailored content for at least one anxiety or depressive symptom).

### Intervention

To inform the development of the program, focus groups were conducted with SSAYA (aged 18 to 25 years) who discussed their experiences regarding their sexual orientation, their mental health needs and their preferences for support services. These data, along with expert review, informed the modification of existing online CBT-based prevention and treatment programs of the National eTherapy Centre. The program content was adapted to be suitable for integrated multiple symptom treatment. In addition, content was personalised for SSAYA, by using inclusive language and content (for example, use of pictures and videos depicting people in same-sex relationships), providing examples of stressors, unhelpful thoughts and beliefs and unhelpful behaviours unique to challenges associated with being same-sex attracted (for example, 'coming out', feeling accepted by heterosexual peers, fear of being assaulted for being gay), providing information on services specialising in supporting same same-sex attracted individuals, providing information on how self-esteem can be affected by being same-sex attracted (for example, through homophobia and internalised homophobia) and strategies to strengthen self-esteem and self-acceptance. Further refinement of the program was undertaken following usability testing, whereby SSAYA reviewed specific modules within the program and made recommendations for amendments to content. This feedback was incorporated where appropriate.

The *Out & Online* program was developed as a standalone resource that should complement face-to-face therapy, but in itself does not require the involvement of a health professional. The program contains seven brief modules containing mental health and wellbeing information and exercises based on CBT principles. The modules contain generic information and information and exercises specific for the symptoms participants endorse in an online assessment at pre-intervention, which screens for generalised anxiety, obsessions and compulsions, posttraumatic stress, specific fear, social anxiety and depressive symptoms. Some program content is also tailored for gender. It is recommended to participants that they spend an hour a week over eight weeks reading through the online modules and practising offline exercises. An eighth module on prevention and help for suicidal thoughts is accessible to all participants at all times.

### Wait-list control group

The intervention is being compared to a wait-list control group so that participants in this group have the opportunity to complete the program. Participants in the wait-list control group will receive access to the intervention program after a 20-week delay. They are able to access any other mental health and wellbeing services during this time.

### Randomisation

An automated computerised randomisation system will generate random sequences for group allocation. This will be based on a permuted blocked (block size = 10) randomisation method to allow for stratification by gender, ensuring that equal gender numbers are allocated to each of the two conditions. Trial enrolment, randomisation and assignment to intervention will all be automated and will not require any human input.

### Administration of assessments

Upon registering on the *Out & Online* website participants will complete baseline assessments (week 0). Automated Email prompts will be sent to participants asking them to complete online assessments at 8 and 20 weeks post-randomisation. In addition, while completing the online program, participants will be prompted by automated Email to complete a survey at weeks 2, 4 and 6 of the 8 week program. Table 1 shows the schedule of assessments for each time point.

**Table 1 Tab1:** **Intended assessments and administration frequency**

Outcomes	Concept	Instrument	Items	Intervention group			Wait-list control group			
				Week 0	Week 8	Week 20	Week 0	Week 8	Week 20	Week 28
Primary	Depressive symptoms	Patient Health Questionnaire-9	9	x	x	x	x	x	x	x
	Generalised anxiety	Generalised Anxiety Disorder-7	7	x	x	x	x	x	x	x
	Panic	Panic Disorder Severity Scale	7	x	x	x	x	x	x	x
	Social anxiety	Social Phobia Inventory	17	x	x	x	x	x	x	x
	Obsessions and compulsions	Obsessive-Compulsive Inventory-Revised	18	x	x	x	x	x	x	x
	Posttraumatic stress	Posttraumatic Stress Disorder Checklist-Civilian Version	11	x	x	x	x	x	x	x
	Specific fear	Fear Questionnaire	16	x	x	x	x	x	x	x
Secondary	Psychological distress	Kessler-10	10	x	x	x	x	x	x	x
	Psychological functioning	*Out & Online* Symptom eScreener	7	x	x	x	x	x	x	x
	Internalised homophobia	Internalised Homophobia Scale-Revised	5	x	x	x	x	x	x	x
	Help-seeking attitudes	Attitudes Toward Seeking Professional Psychological Help Scale	10	x	x	x	x	x	x	x
	Life satisfaction	Satisfaction With Life Scale	5	x	x	x	x	x	x	x
	Locus of control	Multidimensional Health Locus of Control Scales-Form C	18	x			x			
	Wellbeing	Mental Health Continuum Short Form	14	x	x	x	x	x	x	x
Moderators	Demographic factors	*Out & Online* Demographic Questionnaire	24	x			x			
Treatment	Program satisfaction	Intervention Evaluation Questionnaire	14		x					
	Departure	Departure Questionnaire	9							

Note*:* in addition to the above schedule, the Kessler-10 will be administered at fortnightly intervals during program completion.

### Primary outcomes

The primary outcomes being assessed are reduction in anxiety and/or depressive symptoms. Validated questionnaires will be used to measure generalised anxiety (Generalised Anxiety Disorder 7 [46]), panic (Panic Disorder Severity Scale [47]), obsessions and compulsions (Obsessive-Compulsive Inventory-Revised [48]), social anxiety (Social Phobia Inventory [49]), posttraumatic stress (Posttraumatic Stress Disorder Checklist-Civilian Version [50]), specific fear (the Fear Questionnaire [51]) and depressive symptoms (Patient Health Questionnaire-9 [52]). These measures are also being used to determine whether participants are eligible to receive specific symptom content in their tailored online program.

In addition, an online screening device (eScreener) was developed in 2011 to measure anxiety and depressive symptoms. This eScreener will be compared against the validated questionnaires in order to develop a shorter means of determining symptom content for the online program. Once the eScreener is validated future entry to the program will first involve an assessment of psychological distress (with the Kessler-10 scale; K10 [53, 54]), with alternate referral recommendations with people with little or very high distress, and then administration of the eScreener as the sole means of determining symptom relevant content.

### Secondary outcomes

As each participant will receive a different number (between one and three) and combination of symptom content (out of generalised anxiety, panic, social anxiety, obsessions/compulsions, specific fear and depressive symptoms), the K10 [53, 54] will be used as a secondary outcome to evaluate progress at fortnightly intervals during the intervention, and at pre- and post-intervention. As research has revealed a strong association between K10 scores and a current Composite International Diagnostic Interview diagnosis of anxiety and affective disorders [54], this short scale is appropriate for the fortnightly progress evaluations and it will allow us to examine the influence of different program lengths and types on the main outcomes of interest.

Additional secondary outcomes will include life satisfaction (Satisfaction With Life Scale [55]), wellbeing (Mental Health Continuum Short Form [56]), internalised homophobia (Internalised Homophobia Scale-Revised [57]), help-seeking attitudes (Attitudes Toward Seeking Professional Psychological Help Scale [58]) and locus of control (Multidimensional Health Locus of Control Scales-Form C [59]). Demographic and background information will be collected at pre-intervention. Participants in the intervention group will also complete a program evaluation survey, which will include standard items regarding satisfaction with the online intervention.

Participants will have the option to 'opt-out' of the trial by clicking on a link on the website or automated Email and those that do this will be invited to complete a Departure Questionnaire which captures reason for opting out of the study.

### Hypotheses

It is hypothesised that at the post-intervention (week 8) and follow-up (week 20) assessment stages, participants assigned to access the intervention immediately will have fewer anxiety and depressive symptoms than those assigned to the wait-list control group.

In addition, it is hypothesised that at post-intervention and follow-up participants allocated to the intervention group will have less psychological distress, reduced internalised homophobia, greater life satisfaction, wellbeing, greater perception of control over their health, and more positive help-seeking attitudes than participants in the wait-list control group.

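### Locus of control is hypothesised to differ at weeks 8 and 20, but Table 1 schedules the scale at week 0 only, so this part of the secondary hypothesis cannot be tested

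*Protocol article*

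**What the plan says.** Three places in the protocol article treat perceived control over health as something the program should change:

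- Study aims lists among the expected additional benefits a "greater sense of control over their health and greater satisfaction with their lives".
- Secondary outcomes names locus of control and its instrument, the "Multidimensional Health Locus of Control Scales-Form C".
- Hypotheses sets the time points and the direction: "it is hypothesised that at post-intervention and follow-up participants allocated to the intervention group will have less psychological distress", and the same sentence goes on to claim "greater perception of control over their health" relative to the wait-list group.

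Administration of assessments then says "Table 1 shows the schedule of assessments for each time point". In that table the locus-of-control scale (18 items) stands in the secondary-outcome block, with a mark at week 0 in each group and no other mark. The only addition in the table note is that "in addition to the above schedule, the Kessler-10 will be administered at fortnightly intervals during program completion".

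**The concern.** A hypothesis about group differences at weeks 8 and 20 needs measurements at weeks 8 and 20. The schedule provides none for this scale. The between-group analysis in Statistical analyses models change across the pre, post and follow-up assessments, and a variable observed only before the intervention has no change to model. A week 0 difference between randomised groups carries no information about the program's effect.

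At stake is one declared secondary outcome, with a stated directional hypothesis, that would yield no result. An analysis plan cannot repair this later, because the data would never have been collected.

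**Working it through.** No sample size, power or alpha figure enters this point. The check is a reading of Table 1, cell by cell, against the hypothesis.

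**1. Column alignment.** The header gives seven cells per row: intervention weeks 0, 8 and 20, then wait-list weeks 0, 8, 20 and 28. Comparing rows shows whether the blanks are real or a conversion fault:

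| Row | Int. 0 | Int. 8 | Int. 20 | WL 0 | WL 8 | WL 20 | WL 28 |
|---|---|---|---|---|---|---|---|
| Locus of control | x | – | – | x | – | – | – |
| Wellbeing (next row) | x | x | x | x | x | x | x |
| Demographic factors | x | – | – | x | – | – | – |
| Program satisfaction | – | x | – | – | – | – | – |

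The neighbouring rows fall where their content says they should: demographics at baseline only, and satisfaction once, after the program, in the intervention group. The columns are intact, so the blanks in the locus-of-control row belong to the table.

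**2. Hypothesised constructs against the schedule.** The secondary hypothesis covers six constructs:

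| Construct | Week 8, both groups | Week 20, both groups |
|---|---|---|
| Psychological distress | yes | yes |
| Internalised homophobia | yes | yes |
| Life satisfaction | yes | yes |
| Wellbeing | yes | yes |
| Help-seeking attitudes | yes | yes |
| Perceived control over health | **no** | **no** |

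**3. Count.** Post-baseline locus-of-control assessments in Table 1 are 0 of 2 in the intervention group (weeks 8 and 20) and 0 of 3 in the wait-list group (weeks 8, 20 and 28). Estimable between-group contrasts are 0 of 2. One of the six constructs has no post-baseline data.

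**4. Other routes to the data.** The table note adds only the Kessler-10. No other instrument in the document is tied to perceived control over health. The scale is not in Table 1's separate moderator block, which holds only demographic factors, so the table does not present it as a baseline covariate either.

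**5. Burden of adding the scale.** Items already scheduled at week 8:

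- Primary: 9 + 7 + 7 + 17 + 18 + 11 + 16 = 85.
- Secondary: 10 + 7 + 5 + 10 + 5 + 14 = 51.
- Total: 85 + 51 = 136, plus 14 satisfaction items in the intervention group, which makes 150 there.

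Eighteen more items add 18/136 = 13% in the wait-list group and 18/150 = 12% in the intervention group.

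**The case against.** The strongest reply is that Table 1 is not the only text on timing. The Abstract says the secondary outcomes are measured at weeks 0, 8 and 20, and Study design says much the same. Neither makes an exception for locus of control. On that reading the blank cells are a slip in one table row, the live surveys may already contain the scale, and the loss of data is hypothetical.

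Part of this stands. The article does give two schedules, and the conclusion that no data will exist depends on Table 1 being the one that is followed. The general text is weak ground for overriding the table, however. The Study design sentence also lists weeks 2, 4 and 6 for primary and secondary outcomes alike, although the table note places only the Kessler-10 at those fortnightly points, so it cannot be taken as an instrument-level schedule. Table 1 is the specific source, and the text points to it as the schedule. If the general text is right, Table 1 is wrong and still has to be corrected.

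Two further objections are fair in part. Only one component of a six-part hypothesis is affected, in a secondary outcome, and the primary inference is untouched. The added burden is also not negligible: about 12 to 13% more items at week 8, in a trial that allows for follow-up drop-out as high as 70%. That is a reason to decide deliberately between the two remedies below. It is not a reason to leave the contradiction in place.

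**Conclusion.** The concern holds. Under Table 1, the locus-of-control component of the secondary hypothesis cannot be tested: 0 of 2 between-group contrasts are estimable, because neither group has a post-baseline value. The other five constructs and all primary outcomes are unaffected.

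The conclusion assumes that the automated surveys follow Table 1. If they follow the general statements in the Abstract and Study design instead, the data will exist and the error is confined to the table. Either way, the hypothesis, the outcome list and the schedule cannot all be correct as they stand.

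The matter is urgent because Trial status gives 23 July 2014 as the start of recruitment. If a participant was randomised that day, week 8 (56 days) fell on 17 September 2014 and week 20 (140 days) on 10 December 2014. Every participant who passes those points without the scale is a permanent loss for this outcome.

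**What to change.** First check what the live week 8 and week 20 surveys contain.

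- **If the scale is already there:** correct the Table 1 row. This costs nothing further.
- **If it is absent and the surveys can still be changed:** add the 18 items at weeks 8 and 20 in both groups, and at week 28 in the wait-list group to match the other scales, and mark these cells in Table 1. The cost is a minor amendment and 18 items at two surveys per intervention participant (36 in all) and at three per wait-list participant (54 in all). Report how many participants had already passed each time point when the change took effect.
- **If the surveys can no longer be changed, or the added length is judged too great:** remove perceived control from the week 8 and week 20 hypothesis, from the secondary outcomes (text and Table 1) and from the anticipated benefits in Study aims, and describe the scale as a baseline variable. If it is to serve as a moderator, say so explicitly, since the article gives it no such role now. The cost is wording only.
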